### Acupuncture intervention(s)

All of the participants will undergo traditional Chinese medicine (TCM) diagnosis. TCM diagnosis in the great majority of infertile patients is kidney and spleen deficiency, liver *qi* stagnation, dampness, or blood stasis, or multiple diagnoses. Therefore, acupoints for the TEAS and EA groups are chosen according to the TCM dialectical treatment principle and our former experimental results [30]. The main acupoints are bilateral Zusanli (ST36), Sanyinjiao (SP6) and Taichong (LR3) (Figure 1). ST36 is an important health care acupoint of the stomach meridian, which can enhance spleen and stomach function and help generate *qi* and blood. SP6 is the confluent acupoint of foot three (kidney, spleen and liver) *yin* meridians, which can supplement the three *yin*s and can regulate *qi* and blood. LR3 is the liver meridian *yuan*-source acupoint, which can assist SP6 to soothe the liver and regulate *qi* and blood. Bilateral Taixi (KI3) will be added for patients with kidney deficiency, Hegu (LI4) will be added to assist Taichong (LR3) for patients with liver *qi* stagnation, and Fenglong (ST40) is for patients who have too much dampness in the body. Therefore, eight acupoints will be used for treating each patient. The combination of ST36, SP6 and LR3 can guarantee basic regulation of *qi* and blood throughout the body. Subsequent modification according to the syndrome differentiation meets the demand of the highlighted syndrome.

**Figure 1 F1:**
[figure not shown]
Acupoint locations.

The TEAS or EA groups will receive a conventional IVF procedure with the addition of TEAS or EA at acupoints. For the EA group, sterile, disposable needles made in Shanghai (China) will be used to a depth of 5 to 20 mm in the selected acupoints after disinfection. The needles will be 25 to 50 mm in length and 0.3 mm in diameter. The *qi* sensation will be achieved by lifting and thrusting movements combined with needle twirling and rotation. Two homolateral acupuncture needles will be connected to form a circuit containing a HANS-100B stimulator (Nanjing Jisheng Company, China) for 30 min. The TEAS group will use skin electrodes placed on acupoints instead of piercing the skin with needles. The TEAS or EA parameters are as follows: alternating 2/100 Hz frequency wave, moderate 0.8 to 1.0 mA electrical current for EA, and 3 to 5 mA for TEAS with a 30×30 mm skin electrode.

TEAS or EA treatments will start from day 3 of menstruation in the ovarian stimulation cycle once every two or three days, 30 min each for more than two weeks until the day of ET. Women in the control group will receive only the conventional IVF procedure.

In total, two acupuncturists from each hospital with a minimum of two years of clinical experience will participate in this process. Training in the treatment protocol, study intent or treatment aspirations, treatment recording, and an explanation of proposed future monitoring will be provided to the acupuncturists.

### Outcome measures

The primary outcome measure is clinical pregnancy (confirmed by ultrasound scan 5 to 6 weeks after ET demonstrating at least one gestational sac with fetal heart activity).

Secondary outcome measures are live birth (defined as the delivery of one or more living infants, >20 weeks gestation or 400 g or more birth weight), number of oocytes retrieval (OCR) and the total gonadotropin dose used in the ovarian stimulation cycle. Ovarian responses are defined according to three categories: poor response, three or fewer OCR; average response, 4 to15 OCR; hyper-response, more than 15 OCR.

Clinical data will be collected from the IVF center databases and from the patients by following up at 6 and 40 weeks after ET. Data on TEAS or EA safety as well as any adverse events will be collected from the practitioner treatment notes.

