### Quality control

To guarantee the study quality, all of the researchers will be required to attend all of the training classes and pass the training test. They must master all of the details of this trial before performing it. For instance, they must master using the randomization method and filling in the case report form (CRF). The acupuncturists should also master finding the correct points and manipulating the needles and electro-acupuncture apparatus. The assessors should master how to collect and input data accurately and completely.

During the trial, all of the details including all adverse events such as broken needles, bleeding, hematomas, fainting, serious pain, and local infection will be recorded. Serious adverse events will be immediately reported to the principal investigator, and rescue procedures will be initiated immediately.

To ensure trial quality, a clinical monitor designated by the principal investigator will verify all of the process details at regular intervals. Moreover, the monitor will check the authenticity of the data.

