## Discussion

IVF is an option for many infertile women, their families and the public, but because of the relatively low success rate, high cost, and possible latent safety problems, new therapies that can improve pregnancy outcomes are highly desirable.

Acupuncture is a frequently used adjunctive therapy for many diseases. The application of acupuncture to IVF has attracted more doctors and patients. Based on the published data, this study will provide significant evidence for using a new method (TEAS) with IVF to improve reproductive outcomes. Although one trial [28] has already reported that TEAS significantly improved the clinical outcome of ET, stimulus frequency, treatment courses or times can be further optimized. Therefore, with appropriate intervention times (from the time of COH to the day of ET), enough treatment courses (six or seven sessions), syndrome differentiation and treatment according to individual characteristics, TEAS may produce a pleasantly surprising result.

In this protocol, we will select the intervention time from COH to ET, from day 3 of the ovarian stimulation cycle to the day of ET to obtain better results. Reasons for this are as follows: 1) the latest meta-analysis demonstrated that acupuncture at approximately the time of COH is the most suitable; 2) according to the studies of Paulus 2002 [4], Westergaard 2006 [7] and Zhang 2011 [28], acupuncture on the day of ET can significantly improve the reproductive outcome of IVF/ICSI; and 3) correcting the state of infertility caused by long-term insufficiency or imbalance requires enough treatment courses.

The control group was based on the fact that any surface stimulation at acupoints, such as acupressure, can cause a physiological reaction or effect [16]. Thus, the control group will not receive any sham TEAS or acupuncture, and they are included mainly as a control group for providing a baseline pregnancy rate. To avoid the psychological placebo effect, every participant will be informed that the TEAS or EA treatments are safe but that procedure effectiveness is unknown.

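### The only named source of adverse-event data is the TEAS/EA treatment notes, so non-serious events would be ascertained unequally between the active arms and control, and not after transfer

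*Protocol article*

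**What the plan says.** The last paragraph of Outcome measures (protocol article) assigns data sources in two consecutive sentences. The first covers clinical data: "Clinical data will be collected from the IVF center databases and from the patients by following up at 6 and 40 weeks after ET". The second covers safety: "Data on TEAS or EA safety as well as any adverse events will be collected from the practitioner treatment notes". The second sentence reaches beyond device safety to any adverse event, and it names one source.

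That source depends on treatment sessions. Acupuncture intervention(s) says of the third arm: "Women in the control group will receive only the conventional IVF procedure". The Discussion adds: "Thus, the control group will not receive any sham TEAS or acupuncture". In the active arms, sessions take place "once every two or three days, 30 min each for more than two weeks until the day of ET".

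Quality control adds a general promise: during the trial, "all adverse events such as broken needles, bleeding, hematomas, fainting, serious pain, and local infection will be recorded". It also states: "Serious adverse events will be immediately reported to the principal investigator". Neither statement is limited by arm. Neither says from whom, or over what period, non-serious events are to be collected.

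**The concern.** Adverse-event rates can be compared between arms only if events are looked for in the same way in each. Here the one named place to look exists in two arms of three. A woman on TEAS or EA is seen by a practitioner every two or three days and can mention an ordinary event of the IVF cycle, which may then be written down. A control woman with the same event has no corresponding record. The active arms could then show an excess of non-serious events that reflects observation and not treatment.

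The period is the second problem. Anything non-serious that arises after transfer falls outside the notes in every arm.

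This matters because the Discussion says that every participant will be told that TEAS and EA are safe. The trial's own data should be able to bear on that statement against women who had neither.

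**Working it through.** The article states no safety figure to reproduce. The check sets the statements side by side; the arithmetic only shows the extent of the gap.

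**1. Who has the named source?**
- TEAS, 840 women (Sample size): sessions, hence notes.
- EA, 840 women: sessions on the same schedule, hence notes.
- Control, 540 women: no active or sham sessions, hence no treatment notes. This is an inference from the intervention description; the article does not say it outright.
- Share of randomized women without the named source: 540 / (840 + 840 + 540) = 540 / 2,220 = 24.3%.

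Control women do have some contact. Of the TCM work-up the article says: "All of the participants will undergo traditional Chinese medicine (TCM) diagnosis". The acupuncturists also operate the randomization. Both take place before any treatment, and neither is a session with ongoing notes.

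**2. When does the source apply?**
- Treatment lasts about two weeks (opening of Methods/Design) or somewhat more (Acupuncture intervention(s)), ending on the day of transfer. Follow-up is 40 weeks.
- At two weeks: 2 / (2 + 40) = 4.8%. At three weeks (assumption): 3 / (3 + 40) = 7.0%.
- So the notes cover roughly 5% to 7% of observation time in the active arms, and none in control.

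**3. Does Quality control supply what is missing?**
- Serious events: yes in principle, in all arms, through reporting to the principal investigator.
- Non-serious events in control women: recording is promised, no source is named.
- Non-serious events after transfer, any arm: recording is promised, no source is named.
- The examples listed are mostly events that would arise at a treatment session, although the list is illustrative.

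**4. Do the 6- and 40-week contacts supply it?** They apply to all arms, but the article assigns them to clinical data and gives adverse events a different source in the next sentence.

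**5. Direction of the bias.** Suppose a non-serious event has the same true proportion p in all arms, and is captured with probability a in an active arm and c in control. The expected apparent difference is p × a − p × c = p(a − c). Before transfer, a is above zero through the notes, while c has no named source. If a > c, the difference favors control although there is no true effect. The article gives none of p, a or c, so no number of events can be derived.

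**6. What remains comparable?**
- TEAS versus EA up to transfer: the same kind of notes on the same schedule.
- Loss after clinical pregnancy: clinical pregnancies minus those ending in live birth, available by arm because both outcomes are collected in all arms.
- Not recoverable this way: ectopic pregnancy, loss before the scan at 5 to 6 weeks, and ovarian hyperstimulation syndrome. The hyper-response category, more than 15 oocytes, is related to the last of these but is a different measure.

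**The case against.** The strongest case on the other side is that this is a condensed article. Event forms, definitions and windows normally sit in the full protocol and the case report form, which the article mentions. Safety is not a listed outcome, and no between-arm safety test is stated. Quality control promises recording of all events, and a monitor checks the process. Local needle and electrode events have no counterpart in an arm without stimulation, so practitioner notes are the natural place for them.

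Much of this stands. Missing forms and windows are not a fault here, and practitioner notes are right for local events. But the article does not leave the source open. It names one, and extends it to any adverse event. That is a stated choice, and it does not fit the promise made in Quality control.

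A reader might infer more than the documents support:
- *Safety cannot be compared between any arms.* Too broad, since TEAS and EA share the same source up to transfer.
- *The control count will be zero by construction.* Quality control promises recording and serious-event reporting without limit by arm, so what is missing is a named source, not the possibility of an event being recorded.
- *An effect on pregnancy loss could not be seen.* Loss after clinical pregnancy can be derived in all arms.
- *The weeks after transfer are wholly uncovered.* Clinical data are collected then; it is adverse events that have no named source.
- *Only needle events are listed.* The list is illustrative, and fainting, pain and infection are not specific to needling.
- *A set number of excess events in each active arm.* This would need an event rate, and an assumption that practitioners note ordinary IVF events. The article gives neither.

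**Conclusion.** The point holds for non-serious adverse events, active arms against control, and for the period after transfer. The named source is absent for 24% of randomized women, and in the others it covers about 5% of observation time on a two-week treatment period. An active-versus-control comparison built on it would be biased, most plausibly towards more events in the active arms before transfer. The size in events cannot be stated from the documents.

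This rests on two inferences: that women without sessions have no treatment notes, and that notes routinely stop with the last session on the day of transfer. Both follow closely from the text, but the article states neither. The primary and secondary outcomes are unaffected, since their data come from the IVF center databases and the patient contacts in all arms. It should be corrected, but it does not threaten the main result.

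**What to change.** Reconcile Outcome measures with Quality control by stating one adverse-event procedure for the whole trial:

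- One form and one period for all three arms, filled from the IVF center databases and the existing contacts at 6 and 40 weeks after transfer.
- Ectopic pregnancy, early loss and ovarian hyperstimulation syndrome as named items on that form.
- Practitioner notes kept for local needle or electrode events, reported descriptively for TEAS and EA only and not set against control.
- An end to the period for women without a transfer, since both contacts are timed from it. The sample size allows for 2,220 − 1,850 = 370 women lost to canceled cycles or no transfer; the IVF center databases can serve as their source.

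The cost is a few more case report form fields and some data entry, with no added visits or staff. Trial status describes the trial as still preparing to recruit, so the change could be made before the first woman is enrolled.

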### Quality control

To guarantee the study quality, all of the researchers will be required to attend all of the training classes and pass the training test. They must master all of the details of this trial before performing it. For instance, they must master using the randomization method and filling in the case report form (CRF). The acupuncturists should also master finding the correct points and manipulating the needles and electro-acupuncture apparatus. The assessors should master how to collect and input data accurately and completely.

During the trial, all of the details including all adverse events such as broken needles, bleeding, hematomas, fainting, serious pain, and local infection will be recorded. Serious adverse events will be immediately reported to the principal investigator, and rescue procedures will be initiated immediately.

To ensure trial quality, a clinical monitor designated by the principal investigator will verify all of the process details at regular intervals. Moreover, the monitor will check the authenticity of the data.

### Statistical analysis

Baseline subject characteristics are described by descriptive analysis, and the balance among groups or subgroups was assessed by analysis of variance or *χ*^2^-test. To assess effects of TEAS and EA, the *χ*^2^-test will be applied to compare frequencies between groups such as the CPR and LBR, and analysis of variance will be performed to compare continuous parameters (gonadotropin dose for example) between the groups (*α* = 0.05). All of the analyses will be based on both an intention-to-treat analysis (ITT, with all randomized patients) and a treated-per-protocol analysis (TPP, with all randomized patients minus withdrawals). Missing patient data for those that dropped out of the study will be analyzed using the last observation carried forward method. Patients with complete data missing for primary outcomes will be considered as a negative ITT pregnancy result and eliminated in the TPP analysis.

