**Methods/Design:**

To explore the effect of TEAS on the clinical pregnancy rate (CPR) and live birth rate (LBR) compared with real acupuncture and controls in women undergoing IVF, a multicenter, randomized controlled trial will be conducted. The inclusion criteria are the following: infertile women <40 years of age undergoing a fresh IVF or intracytoplasmic sperm injection cycle, and the study will be restricted to women with the potential for a lower success rate as defined by two or more previous unsuccessful ETs (fresh or frozen). Those who have severe illnesses possibly precluding IVF or pregnancy, have FSH levels greater than 20 IU/L, received donor eggs, had been previously randomized for this study or had undergone acupuncture (in any modality) as infertility treatment will be excluded. The subjects will be randomly assigned to the TEAS group (IVF + TEAS), the electro-acupuncture (EA) group (IVF + EA), or the control group (only IVF). A total sample size of 2,220 women is required to detect differences in CPR among the three groups. TEAS or EA treatments will start once every two or three days from day 3 of menstruation in the ovarian stimulation cycle until the day of ET. The parameters of TEAS or EA will be the following: a frequency of 2/100 Hz, a moderate electrical current of 3 to 5 mA for TEAS and 0.8 to 1.0 mA for EA. The primary outcome is CPR. Secondary outcomes are LBR, the number of oocytes aspirated and the total gonadotropin dose used in the stimulation cycle.

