### Sample size

Sample size calculation is based on the increased range of CPR from acupuncture as described in previous studies (13% to 18% based on the following studies: Stener-Victorin, 17.6% [3]; Paulus, 16.2% [4]; Westergaard, 16% [7]; Dieterle, 18% [8]; and Sator-Katzenschlager, 13.5% [25]). Smith CA chose a conservative 7% estimate based on their previous study [27]. The increased range of clinical effects from TEAS compared with the control group was 13.4% to 20.7% [28]. Therefore, we estimated a 7% increase for the EA group and a 15% increase for the TEAS group compared with the control group. The possible proportion of women with a clinical pregnancy for women with two or more cycle failures in the control group was 20% [27]. To detect differences using a pairwise comparison method, the sample size should be 1,850 according to optimum allocation (700 for the TEAS group, 700 for the EA group, and 450 for the control group) using the Shieh-O'Brien approximation method assuming that alpha (two-sided) is 0.05, the overall power is 0.90, the power between the TEAS and EA groups is 0.80, and the power between the EA and control group is also 0.80. A total sample size of 2,220 women (840 for the TEAS group, 840 for the EA group, and 540 for the control group) is required allowing for a 20% loss due to canceled cycles or no ET.

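### Clinical pregnancy is compared pairwise among three arms at alpha 0.05 with no stated order or split of alpha, so as written the family-wise error is about 9% to 12%; testing the three-group chi-square first would hold it at 5%

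*Protocol article*

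**What the plan says.** The Outcome measures section names one primary endpoint: "The primary outcome measure is clinical pregnancy". The Abstract gives the aim of the sizing: "A total sample size of 2,220 women is required to detect differences in CPR among the three groups". The Sample size section states the structure, "To detect differences using a pairwise comparison method", and the error and power targets, "assuming that alpha (two-sided) is 0.05, the overall power is 0.90, the power between the TEAS and EA groups is 0.80", with 0.80 also for EA against control. The planning rates are 20% in control, 27% with EA (7 points more) and 35% with TEAS (15 points more). The evaluable numbers are 700, 700 and 450, raised to 840, 840 and 540.

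The Statistical analysis section then provides that the chi-square test "will be applied to compare frequencies between groups such as the CPR and LBR" and that analysis of variance be used for continuous measures, with a single alpha of 0.05. All analyses are done in both the intention-to-treat (ITT) and the per-protocol (TPP) populations. No order of tests, primary pair or division of alpha is given.

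**The concern.** Three arms give three pairs: TEAS against control, EA against control, and TEAS against EA. If each may be tested at 0.05 and a significant result in any of them supports a claim on the primary outcome, the chance of a false claim exceeds the 5% that the stated alpha suggests. The trial is presented as evidence for a new method, so the error rate behind a positive statement about TEAS or EA matters.

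This is more than detail left to an analysis plan. The article itself fixes the alpha, the pairwise structure and the test, and together these do not deliver a 5% error rate.

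**Working it through.** **Inputs.** From the Sample size section: two-sided alpha 0.05; rates 0.35 (TEAS), 0.27 (EA), 0.20 (control); n = 700/700/450 evaluable and 840/840/540 randomised. From the Statistical analysis section: chi-square tests at 0.05.

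**1. The plan's own power figures.** Pooled two-proportion test: power = Φ[(d − z·s0)/s1]. Here d is the difference in rates, s0 the standard error under the null, s1 the standard error under the alternative, and z = 1.96 at alpha 0.05.

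- TEAS against EA: d = 0.08, s0 = 0.02472, s1 = 0.02463. (0.08 − 1.96 × 0.02472)/0.02463 = 1.281, so power is 0.90 (stated: 0.80).
- EA against control: d = 0.07, s0 = 0.02590, s1 = 0.02524. (0.07 − 1.96 × 0.02590)/0.02524 = 0.762, so power is 0.777 (stated: 0.80). Other approximations give 0.778 to 0.792.
- Overall 2-df test: mean rate 0.2832, noncentrality Σn(p − 0.2832)²/(0.2832 × 0.7168) = 31.3, so power is 0.9995 (stated: 0.90).

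With alpha/3 = 0.0167 (z = 2.394), TEAS against EA has power 0.801, which matches the stated 0.80. EA against control then falls to 0.624. No single alpha reproduces both pairwise powers. The EA-control sizing fits an unadjusted 0.05; the TEAS-EA sizing also fits a three-way split.

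**2. Family-wise error with no order or split.** The pairwise statistics share arms and are correlated, so 1 − 0.95³ = 14.3% is too high. At 700/700/450 the two comparisons with control have correlation (1/450)/(1/700 + 1/450) = 0.61. TEAS-EA and EA-control have correlation −0.44. One million simulated trials per sample size, with 20% in every arm and each pair tested at |z| > 1.96, give:

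| Pairs that may be claimed | 700/700/450 | 840/840/540 |
|---|---|---|
| All three | 12.2% | 12.2% |
| The two with a stated power | 9.2% | 9.3% |
| The two against control | 8.7% | 8.7% |

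The bivariate normal calculation for the two-pair cases at 700/700/450 gives 9.2% and 8.7%, in agreement.

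**3. Overall test first.** Requiring the 2-df chi-square to exceed 5.99 before any pair is read gives 5.0% at both sample sizes. If instead two arms are equal and the third differs, only one null hypothesis is true and its own 5% test bounds the error. With three arms these are the only cases, so the procedure is closed.

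**4. Power cost at 700/700/450 (simulated, without → with the overall test first).**

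| True rates TEAS/EA/control | TEAS-EA | EA-control | TEAS-control |
|---|---|---|---|
| 35/27/20% (planned) | 90.0 → 90.0% | 78.0 → 78.0% | 99.99 → 99.96% |
| 27/27/20% | no difference | 78 → 71% | 78 → 71% |
| 27/23.5/20% | 33 → 31% | 29 → 27% | 78 → 67% |

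For comparison, a three-way Bonferroni split under the planned rates would leave about 80% for TEAS-EA and 62% for EA-control.

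**The case against.** The strongest counter-argument is that an overall test may already be intended. The Sample size section lists an overall power of 0.90 apart from the two pairwise powers, and the Abstract speaks of differences among all three groups. In the analysis section the chi-square test stands beside analysis of variance, which on three arms is an overall test. The word pairwise appears only in the sample-size text. On this view the article needs a clarification, and a condensed article may leave the order of tests to its analysis plan.

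Much of this stands. A reader might infer that the protocol commits to testing each pair at its own unadjusted 0.05. The documents do not support that: one alpha is given, no sentence says how it applies to each pair, and the TEAS-EA sizing is also compatible with a split alpha. A reader might also take 12% as the error rate. That counts all three pairs, whereas powers are stated for only two, and on two pairs it is about 9%.

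What does not stand is that the present text protects the 5% level. An overall power figure is not a rule that the overall test must succeed before the pairs are read. Every reading that allows claims from more than one pair at 0.05 exceeds 5%.

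Two related worries add little. ITT and TPP are two analysis sets of one outcome and are not part of the 9% to 12%. Live birth, oocyte number and gonadotropin dose are already labelled secondary.

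**Conclusion.** The point holds at moderate severity. As written, the family-wise error for clinical pregnancy is about 12% with three claimable pairs and about 9% with two. This assumes no true difference between arms, 0.05 for each pair, and that any significant pair supports a claim. Testing the three-group chi-square first brings it to about 5%.

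It would go too far to call the change free or the flaw one that must be fixed before the trial can proceed. The absence of a power cost depends on the planned 35/27/20%. With smaller effects, power against control can fall by 7 to 11 points in the cases shown. The power figures use evaluable numbers. The mismatch between stated and recomputed powers is a separate matter and does not change the error-rate result.

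**What to change.** Add one sentence to the Statistical analysis section: for clinical pregnancy in the ITT population, the three-group chi-square test (2 df) is performed first at two-sided 0.05, and the three pairwise chi-square tests are read at 0.05 only if it is significant; the TPP analysis is supportive. State in the Sample size section that the pairwise powers refer to this procedure.

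This needs no extra patients or data. Enrolment had not begun when the article was written, so the rule can be set before any outcome is seen. The price is some power against control if the true effects are smaller than planned, as tabulated above.

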### Eligibility criteria

Women presenting to the reproductive medicine center of the involved hospitals will be screened for fitness to undergo IVF. All of the women with an indication for IVF, such as tubal infertility, severe male factor infertility, severe endometriosis, unexplained infertility, immune infertility, and anovulatory infertility, will be informed of the study.

The inclusion criteria are the following: (1) infertile women <40 years of age undergoing a fresh IVF or intracytoplasmic sperm injection (ICSI) cycle; (2) who have a potentially lower success rate, which is defined as two or more previous unsuccessful ETs (fresh or frozen); (3) who are willing to sign an informed consent form indicating that they are aware of the investigational nature of this study, which is in keeping with the institutional policies; and (4) who are willing to return to the study site for visits. The inclusion criteria were necessary because women who have experienced several unsuccessful OAs or ETs may easily accept randomization into this study, and adding TEAS or EA may significantly improve their clinical outcomes.

The exclusion criteria are the following: (1) have major medical illnesses (such as stage III heart disease, severe hypertension, uncontrolled diabetes mellitus, positive HIV status, severe bleeding dyscrasias, *etcetera*) possibly precluding IVF or pregnancy; (2) have FSH levels greater than 20 IU/L; (3) have received donor eggs; (4) have cutaneous lesions within the acupoint area; and (5) had previously participated in this study or previously undergone acupuncture (in whatever modality) as infertility treatment.

The withdrawal criteria are the following: (1) a patient is deemed unfit for the inclusion criteria; (2) early discontinuation for any reason (for example, consent withdrawal, adverse events, and treatment failure); (3) the patient does not strictly abide by the intervention protocol or uses other methods beyond the project that may affect pregnancy outcome; and (4) complete data missing for primary outcomes.

Patients have the right to decline participation in the study, and they may withdraw their consent at any time. Their consent or refusal to consent will not affect their expected IVF intervention.

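### ITT and per-protocol analyses have equal standing, and the per-protocol set drops women for undefined treatment failure and non-adherence, which can bias it between unblinded arms

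*Protocol article*

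**What the plan says.** All references are to the protocol article.

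- **Analysis sets (Statistical analysis).** "All of the analyses will be based on both an intention-to-treat analysis (ITT, with all randomized patients") and on "a treated-per-protocol analysis (TPP, with all randomized patients minus withdrawals"). Neither set is named as primary.
- **Who counts as withdrawn (Eligibility criteria).** There are four grounds. The first is being found ineligible. The second is "early discontinuation for any reason (for example, consent withdrawal, adverse events, and treatment failure"). The third is that "the patient does not strictly abide by the intervention protocol or uses other methods beyond the project that may affect pregnancy outcome". The fourth is a missing primary outcome. Treatment failure is not defined anywhere.
- **Missing primary outcome (Statistical analysis).** These women "will be considered as a negative ITT pregnancy result and eliminated in the TPP analysis".
- **What each arm can deviate from (Acupuncture intervention(s)).** TEAS and EA women attend 30-minute sessions every two or three days for more than two weeks, up to embryo transfer (ET). By contrast, "Women in the control group will receive only the conventional IVF procedure".
- **Blinding (Randomization and blinding).** Patients and acupuncturists know the allocation; the outcome assessor and the statistician do not.

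**The concern.** A per-protocol set that removes every withdrawal inherits whatever drives withdrawal. Two of the stated grounds can be tied to prognosis. Treatment failure, if it covers events such as a poor ovarian response or a cancelled cycle, is a step towards not becoming pregnant. Session non-adherence may also follow a cycle that is going badly, because a woman who expects to fail has less reason to keep attending. That second route exists only in the TEAS and EA arms, and the decision to stop is taken by people who know the arm.

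If non-pregnant women leave the TEAS or EA denominator more often than the control denominator, the per-protocol pregnancy rate rises in the active arm without any treatment effect. ITT and per-protocol can then disagree, partly because missing outcomes count as failures in one and disappear from the other. The article does not say which result answers the primary question. That choice should be fixed before outcomes are seen, and the Trial status section places the trial before recruitment.

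**Working it through.** **Inputs from the article (Sample size).** Control clinical pregnancy rate 20%; planned gains of 7 points (EA) and 15 points (TEAS); two-sided alpha 0.05; randomised numbers 840 TEAS, 840 EA and 540 control. The randomised numbers reproduce from the evaluable ones with a factor of 1.20: 700 × 1.20 = 840, 450 × 1.20 = 540, and 1,850 × 1.20 = 2,220.

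**Inputs that are assumptions.** The article gives no withdrawal rate by arm and no pregnancy rate among withdrawn women. Its 20% loss refers to cancelled cycles or no ET. I therefore take withdrawn shares of 10% and 20% of one active arm, and pregnancy rates among withdrawn women from 20% (withdrawal unrelated to prognosis) down to 0%.

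**Step 1, shift in the per-protocol rate.** With true rate p, withdrawn share f and pregnancy rate q among the withdrawn:

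per-protocol rate = (p − f·q) / (1 − f)

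- f = 0.10, q = 0.05: (0.20 − 0.005) / 0.90 = 21.7%
- f = 0.20, q = 0.05: (0.20 − 0.010) / 0.80 = 23.75%
- f = 0.10, q = 0: 0.20 / 0.90 = 22.2%
- f = 0.20, q = 0: 0.20 / 0.80 = 25.0%
- q = 0.20, any f: 20.0%, no shift

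**Step 2, type I error of one active arm against control when the true rate is 20% in both.** With d the expected per-protocol difference, s0 the pooled and s1 the unpooled standard error:

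P(reject) ≈ Φ((d − 1.96·s0)/s1) + Φ((−d − 1.96·s0)/s1)

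Worked case, f = 0.10 and q = 0.05, no controls withdrawn:
- Active n = 840 × 0.90 = 756; control n = 540; d = 0.0167.
- Pooled rate = (756 × 0.2167 + 540 × 0.20) / 1,296 = 0.2097.
- s0 = 0.0229, s1 = 0.0228.
- P(reject) = Φ(−1.24) + Φ(−2.70) = 0.1075 + 0.0035 = 0.111.

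| Active withdrawn | Control withdrawn | Pregnancy rate among withdrawn | Per-protocol rates, active vs control | Type I error |
|---|---|---|---|---|
| 10% | 0% | 20% | 20.0% vs 20.0% | 0.050 |
| 10% | 0% | 5% | 21.7% vs 20.0% | 0.111 |
| 10% | 0% | 0% | 22.2% vs 20.0% | 0.16 |
| 20% | 0% | 5% | 23.75% vs 20.0% | 0.345 |
| 20% | 0% | 0% | 25.0% vs 20.0% | 0.54 |
| 10% | 5% | 5% | 21.7% vs 20.8% | 0.066 |
| 20% | 10% | 5% | 23.75% vs 21.7% | 0.131 |
| 20% | 20% | 5% | 23.75% vs 23.75% | 0.050 |

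Simulation with 840 against 540 women agrees for the rows with a 0% pregnancy rate among the withdrawn (0.159 and 0.544), and gives 0.050 when nobody is removed, as in ITT.

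**Step 3, scale against the planned effect.** To create the 7-point EA gain from nothing, the removed share w of non-pregnant women must satisfy 0.20 / (1 − w) = 0.27, so w = 1 − 0.20/0.27 = 25.9%, or about 218 of 840. The bias is thus unlikely to imitate the whole planned effect, but it need not do so to produce a significant result.

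**The case against.** The strongest reply has four parts.

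**Exclusion is not unequal by design.** A reader might infer that only TEAS and EA women can be removed. The text does not support that. The non-adherence ground also covers use of other methods outside the project, which unblinded controls could seek. Ineligibility, consent withdrawal, treatment failure and missing outcomes can remove controls too. Only session non-adherence is specific to the active arms. This part stands.

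**Treatment failure need not mean no pregnancy.** A reader might equate the two. The article gives the term only as an example of early discontinuation. Sessions end on the day of ET, while clinical pregnancy is confirmed 5 to 6 weeks later, so a negative scan cannot be what stopped the sessions. The reading as a precursor of the outcome is plausible, but the term is undefined and such precursors occur in all arms. This part also stands. It narrows the mechanism without removing it.

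**The large error rates are corner cases.** A woman who merely misses sessions still has IVF and may have an ordinary chance of pregnancy; at 20% among the withdrawn there is no bias. This is correct, and the figures can only be shown as a range.

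**ITT is already planned, and ranking of analysis sets may be left to a fuller document.** ITT with missing outcomes counted as negative is sound here, and reporting both sets would expose a disagreement. Nothing says that a claim may rest on the per-protocol result alone; that would be inferred from silence. Still, the article does more than omit detail. It states an exclusion rule that can select on prognosis and places the resulting set beside ITT for all analyses.

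**Conclusion.** The point holds in limited form. The article sets ITT and per-protocol side by side without saying which decides clinical pregnancy, and its per-protocol rule can remove women for reasons related to prognosis, at rates that can differ between unblinded arms. The per-protocol comparison with control can therefore be biased, possibly in favour of TEAS and EA.

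Its size cannot be known from the article. Across the assumed scenarios the type I error of one active-versus-control comparison runs from 0.05 (withdrawal unrelated to prognosis, or equal removal in both arms) to 0.54 (20% of the active arm removed, none of them pregnant, no controls removed). Where controls withdraw at half the active rate and 5% of withdrawn women are pregnant, it is 0.066 to 0.131. These figures assume a true rate of 20% in both arms and the planned numbers randomised.

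The article does not establish that bias will occur, that it must favour the active arms, or that the trial's conclusion will rest on the per-protocol set.

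**What to change.** In the Statistical analysis section:

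1. Name ITT as the single primary analysis for clinical pregnancy: all randomised women, as allocated, with missing outcomes counted as not pregnant. Call the per-protocol analysis supportive only.
2. Separate the per-protocol exclusions from the withdrawal list. Do not exclude a woman from that set for treatment failure or for another outcome-related reason such as a cancelled cycle or no ET. Define treatment failure where the term is kept. This concerns who is analysed, not when treatment is stopped.
3. Report per-protocol exclusions by arm and by reason, and state that session adherence can exclude women only from the TEAS and EA arms, so that the set is read with that asymmetry in view.

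The cost is wording only: no additional patients, visits or data.
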